#### 2. The TRIMS randomised controlled trial

##### Participant recruitment

Local ethics and research governance approvals were obtained prior to conducting the main TRIMS RCT. General practices (in Leicestershire, UK) who were already taking part in local population based diabetes screening studies [41-43] were approached to participate. Potential participants aged 40 - 74 years, from volunteer practices, were then recruited by postal invitation using two different recruitment strategies. Firstly, eligible people identified as having MetS (International Diabetes Federation (IDF) definition [6]) according to their previous screening results, were sent a postal invitation via their GP. Secondly, people who had consented to be approached with details of other research studies, when they participated in a screening study, and who met the inclusion criteria were sent a letter of invitation by the principal investigator of the screening study. Exclusion criteria included previous history of T2DM or CVD; pregnancy and/or breast feeding; life-limiting terminal illness; lack of capacity to give informed consent; being housebound or residing in a nursing/care home; and inability to understand, speak and read English.

Respondents were asked to attend for an initial appointment having fasted overnight for at least 8 hours. Written informed consent was obtained from volunteers by a research nurse prior to carrying out any tests or measurements. Participants underwent a 75 g oral glucose tolerance test (OGTT) [44], and had additional demographic and bio-medical data collected in a standardised way, according to the schedule in Table 4. Data collected included measurements to confirm eligibility and MetS status; however, if relevant blood tests for glucose and lipids had been conducted for screening within the last 3 months these were not repeated and the initial screening values were used as the baseline values.

**Table 4 T4:** Data collection schedule and outcome measures

Collected by research nurse	Baseline	6 months	12 months
Bloods & biomedical data			
FPG	✓	✓	✓
2 hour glucose	✓	✓	✓
HbA1c	✓	✓	✓
Total cholesterol	✓	✓	✓
HDL	✓	✓	✓
Triglycerides	✓	✓	✓
Albumin:creatinine ratio (urine)	✓	✓	✓
Blood pressure	✓	✓	✓
Waist circumference	✓	✓	✓
Hip circumference	✓	✓	✓
Height	✓	✗	✗
Weight	✓	✓	✓
Medical history	✓	✓	✓
Current medication	✓	✓	✓
Smoking status	✓	✓	✓
Biomarkers			
Insulin, Hs-CRP, Adiponectin	✓	✗	✓
Demographic details			
Age	✓	✗	✗
Sex	✓	✗	✗

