###### Primary and secondary outcomes

The primary outcome is reversal of MetS according to the IDF criteria in the intervention group compared to the control group, after 12 months of follow-up. Taking into account the ethnic diversity within our target population, the IDF criteria were chosen in preference to the National Cholesterol Education Panel (NCEP) definition due to the provision of ethnic specific cut points for waist circumference and central obesity (Table 5). Secondary outcomes compared at baseline versus 12 months, and for the intervention group versus the control group, see Table 4, include changes in: i) the prevalence of MetS according to NCEP criteria; ii) individual components of the MetS (fasting plasma glucose, triglycerides, high density lipoprotein cholesterol (HDL), blood pressure, waist circumference), and 2 hour glucose.

**Table 5 T5:** The International Diabetes Federation (IDF) and updated National Cholesterol Education Panel (NCEP) definitions of metabolic syndrome.

**NCEP (2005)**[37]	**IDF (2005)**[6] ESSENTIAL REQUIREMENT **Central obesity** **Waist circumference** >94 cm^† ^(males) >80 cm^† ^(females)
*ANY 3 out of the following 5* ↓	***+ ****ANY 2 out of the following 4* ↓
**1) Raised fasting plasma glucose:** ≥ 5.6 mmol/l*	**1) Raised fasting plasma glucose:** ≥ 5.6 mmol/l
**2) Raised triglycerides:**** ≥ 1.7 mmol/l and/or **3) Low HDL cholesterol:**** < 1.03 (males) < 1.29 (females)	**2) Raised triglycerides:** ≥ 1.7 mmol/l *(or specific treatment for)* and/or **3) Reduced HDL cholesterol** < 1.03 (males) < 1.29 (females), *(or specific treatment for)*
**4) Hypertension:**** Blood pressure ≥ 130/85 mmHg	**4) Raised blood pressure:** Blood pressure ≥ 130/85 mmHg (or treatment for previously diagnosed hypertension)
**5) Central obesity:** Waist circumference > 102 cm (males) > 88 cm (females)	
*Updated from the original NCEP 2001 definition *[5]: *previous fasting plasma glucose value (≥6.1 mmol/l) was updated to include a lower value; *** was updated to include drug treatment *.	*^†^Waist circumference ethnic-specific for Europid men & women; Waist circumference for South Asians (Chinese, Malay, & Asian Indian): ≥90 cm (males), & ≥80 cm (females)*.

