Around half of all participants were prescribed a statin and/or antihypertensive at baseline. However, this was similar for both intervention and control group participants. We acknowledge that compliance could change during the study period but this could be a possible benefit of the intervention. In addition, it is recognised that prescribing may change, including new prescriptions for lipid or blood pressure medication to those who were medication naïve at baseline. This would then result in no change in the appropriate MetS criterion. However, prescribing changes will occur in a "real world setting" and are likely to occur in both groups. We are recording prescription medications at baseline, 6 months and 12 months and we will also consider looking at prescription records at the end of the study. Furthermore, our planned analysis using multi-variable regression methods will allow us to consider adjustment for prescribed medication.

We recognise that the majority of previous epidemiological studies and clinical trials have used the NCEP definition [5,37] to identify MetS. However, bearing in mind the ethnic diversity in our study population, provision of ethnic-specific cut-off points for waist circumference and central obesity within the IDF definition [6] led to preferential selection of this definition for our trial. Additionally, secondary outcome measures for the study include the prevalence of MetS according to NCEP criteria at 12 months follow-up compared to baseline.

We acknowledge that our study excluded people who were unable to understand, speak and read English. However, our study population includes a subset of the SA population in the UK (English speaking people mainly of Indian origin), and overall 22% of participants were of SA ethnicity. Additionally, we took steps to address cultural needs, for example by including foods commonly eaten in the SA community. If the education programme is found to be successful we will consider adapting it for non-English speakers and ethnically diverse populations. However, we acknowledge that additional work would need to be conducted to test for transferability of the intervention to other settings and populations.

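### Table 5 gives the glucose criterion no treatment clause, so a participant who starts glucose-lowering medication can be scored as having reversed metabolic syndrome

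*Protocol article*

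**What the plan says.** The section on primary and secondary outcomes sets the endpoint: "The primary outcome is reversal of MetS according to the IDF criteria in the intervention group compared to the control group, after 12 months". Table 5 in that section defines IDF MetS as central obesity plus any two of four further components:

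- Triglycerides and HDL: a cut-off, "or specific treatment for" the abnormality.
- Blood pressure: a cut-off, "or treatment for previously diagnosed hypertension".
- Glucose: the "Raised fasting plasma glucose" row reads "Raised fasting plasma glucose: ≥ 5.6 mmol/l", and nothing more.

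The NCEP definition, a secondary outcome, follows the same pattern. The footnote saying that a criterion "was updated to include drug treatment" is attached to triglycerides, HDL and hypertension. The glucose row carries only the note on its lowered cut-off.

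The recruitment section says "Exclusion criteria included previous history of T2DM or CVD", a restriction on history at entry. The Discussion considers new lipid or blood pressure prescriptions during follow-up and concludes: "This would then result in no change in the appropriate MetS criterion". The article does not say how a participant who starts glucose-lowering medication during follow-up is classified. Table 4 schedules medical history, current medication, fasting glucose and 2-hour glucose at baseline, 6 and 12 months.

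**The concern.** Three of the four components treat a drug-controlled abnormality as still present. The fourth treats it as gone. For lipids and blood pressure, the Discussion accepts that starting a drug does not make a criterion disappear. Table 5 as printed does not extend that logic to glucose.

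Preventing type 2 diabetes is a stated aim, and the Background puts the diabetes risk of people with MetS at 3.5 to 5 times the usual. A scoring rule under which starting diabetes medication can help a participant count as a success therefore works against the trial's purpose. It could also act unevenly. The Randomisation section says that intervention participants were to receive their biomedical results as part of the education, while controls had to ask their GP, so detection and treatment might differ by arm.

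**Working it through.** **1. The plan's own figure.** Inputs from the Sample size section: MetS in 90% of controls and 60% of the intervention arm, alpha 0.05 (taken as two-sided), power 0.80, 20% loss.

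n per arm = [1.960 × √(2 × 0.75 × 0.25) + 0.842 × √(0.9 × 0.1 + 0.6 × 0.4)]² / 0.30² = (1.200 + 0.484)² / 0.09 ≈ 31.5, so 32. Then 32 / 0.80 = 40 per arm and 80 in total, as stated. The scoring gap does not alter this figure.

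**2. Applying Table 5 as printed.** Take a participant with a waist above the cut-off, raised glucose and one other component, so 2 of 4 and MetS present.

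| Change by 12 months | Components met | Scored as |
|---|---|---|
| Starts glucose-lowering medication, fasting glucose below 5.6 mmol/l | 1 of 4 | reversed |
| The other component is blood pressure; drug treatment for diagnosed hypertension brings it below the cut-off; glucose still raised | 2 of 4 | MetS |
| The other component is a lipid; specific treatment brings it within range; glucose still raised | 2 of 4 | MetS |

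If the waist falls below the cut-off, MetS is absent whatever the glucose row says, so the gap matters only while the waist requirement is met.

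**3. How many could be exposed.** Inputs from Table 6 and the Results.

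- Consistency of the counts: 73 + 22 + 72 + 67 = 234 components met, and 25 × 2 + 44 × 3 + 13 × 4 = 234. By arm: intervention 37 + 12 + 35 + 35 = 119 = 13 × 2 + 23 × 3 + 6 × 4; control 36 + 10 + 37 + 32 = 115 = 12 × 2 + 21 × 3 + 7 × 4.
- Everyone meeting all five criteria meets glucose. That leaves 22 − 13 = 9 glucose-positive participants with three or four criteria: 12 − 6 = 6 intervention and 10 − 7 = 3 control.
- Glucose is pivotal only for those with exactly three criteria (waist, glucose and one more). The ceiling is therefore 9/82 = 11%.
- Listing every pattern of components that fits the published totals gives 0 to 6 pivotal participants in the intervention arm and 0 to 3 in control. Zero is compatible with the data.

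This covers the direct route only. Someone glucose-negative at baseline, or with more components, could also be affected if other components were lost while diabetes developed and was treated.

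**4. Effect on the test.** At the planning assumptions with 32 evaluable per arm, MetS is present in about 0.60 × 32 = 19.2, so 19, versus 0.90 × 32 = 28.8, so 29. The continuity-corrected chi-squared test is used because it reproduces Table 6 (sex 0.359, glucose 0.908, triglycerides 0.917).

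| MetS, intervention vs control (of 32 each) | p |
|---|---|
| 19 vs 29 | 0.009 |
| 20 vs 29 (one intervention case rescored as MetS) | 0.018 |
| 21 vs 29 (two rescored) | 0.034 |

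The conclusion does not change with one or two cases.

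**The case against.** The strongest reply is that Table 5 condenses cited definitions and that the full protocol may say more. The sources are not at hand, so this point makes no claim about what they contain. It stands on the table as printed, which spells out treatment clauses for three components and none for the fourth. That is a stated rule, not an omitted detail.

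The Discussion's remark on prescribing is also not exhaustive: lipid and blood pressure drugs are named as included examples, and adjustment for medication in regression is left open for any class. That stands, but adjustment does not change how an outcome is scored.

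The chain of events needed is long: drug treatment started within 12 months, fasting glucose below 5.6 mmol/l, and fewer than two other components met. The other three were each met by 82% to 89% of participants at baseline. Half were on a statin and half on an antihypertensive (42 of 82 each), so treatment clauses tend to hold those components in place. This limits the size of the point substantially.

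Three stronger readings are tempting, and the documents do not support them:

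- *Diabetes found at the baseline glucose tolerance test enters the trial by this route.* That test preceded randomisation, baseline measurements served to confirm eligibility, and 82 of 129 volunteers were enrolled. The flow chart is not shown, so whether such cases were excluded cannot be told.
- *A single case could decide the trial.* That needs a chosen borderline result. For example, 20/32 vs 28/32 gives p = 0.043, and 21/32 vs 28/32 gives 0.077, but without continuity correction these are 0.021 and 0.039. At the planning rates nothing crosses 0.05.
- *Any diabetes diagnosis should count as meeting the criterion, at no cost.* That would hide normalisation achieved by lifestyle alone and would bring any difference between arms in diagnosis into the primary endpoint. The other Table 5 clauses turn on treatment.

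**Conclusion.** The point holds as a minor defect in the outcome definition. Among the four additional IDF components in Table 5, glucose alone has no treatment clause, and the NCEP column shares the gap. Waist has none either, but it is a body measurement and the essential requirement. Applied literally, the rule can score a participant on glucose-lowering medication as reversed, against both the prevention aim and the Discussion's own reasoning on treatment.

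The likely effect is very small. By the direct route at most 9 of 82 participants could be exposed, possibly none, and only those who then start treatment would be misclassified. The article gives no diabetes incidence, so the number of treated cases is unknown; the one or two cases used in the working are an assumption. The sample size is unaffected. The conclusion rests on Table 5 being the rule actually applied at 12 months.

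**What to change.** Add one line to the outcome definition, for the IDF and NCEP versions alike and for outcome scoring only: at 6 and 12 months the glucose criterion is met if fasting glucose is at least 5.6 mmol/l or the participant is taking glucose-lowering medication. This puts glucose on the same footing as the other three components. Report incident type 2 diabetes by arm beside the primary result. Count diagnosed but untreated diabetes as meeting the criterion only in a sensitivity analysis.

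No new data are needed, since medication, medical history and glucose are already collected at both follow-up visits (Table 4). The cost is a slight departure from the definition as printed, which should be stated; scoring by the printed table can be shown alongside.

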###### Data collection and assessment of outcomes

Routine laboratory methods were used for all biochemical measurements. Serum total cholesterol, HDL cholesterol, and triglycerides; plasma fasting and 2-hour glucose; and urine albumin and creatinine, were measured using a Siemens Adiva 2400 analyser (Siemens Healthcare Diagnostics, Camberley, UK). Glycated haemoglobin (HbA1c) was measured using a Tosoh G7 analyser (Tosoh Bioscience Ltd, Redditch, UK). Low density lipoprotein cholesterol (LDL) was estimated using the Friedewald equation[45]. If participants gave consent, additional blood was taken at baseline (and 12 months) for measurement of bio-markers that are linked to MetS (high-sensitivity- C-reactive protein (hs-CRP), adiponectin and insulin)[46]. After processing, the serum for bio-markers was stored in aliquots at -80°c and these samples will be analysed as a single batch at the end of the study.

Resting blood pressure was measured using an Omron automatic blood pressure monitor, (Omron Healthcare UK Ltd) and a mean value was calculated from the last 2 measurements in a series of three. Waist circumference was measured midway between the costal margin and the iliac-crest, in the mid-axillary line, over minimal clothing and at the end of expiration, and was recorded to the nearest mm. Hip circumference was measured at the widest point over the buttocks and to the nearest mm. Weight in light clothing and no shoes was recorded to the nearest 0.1 kg using a digital scale, and height to the nearest cm using a stadiometer and with head placed in the Frankfurt plane. Additional data were collected on physical activity [47], anxiety and depression [48], quality of life [49], dietary habits [50] and self-efficacy [51] using validated questionnaires that were self-completed by participants, as outlined in Table 4. Ambulatory activity was measured using a CW-700 Yamax Digi-Walker electronic pedometer with a 7-day memory (Yamax Corporation, Tokyo, Japan) and an average step count per day was calculated from measurements from at least 3 days.

#### Follow-up data collection

The control and intervention groups will be recalled at 6 months and 12 months for repeat measurements (Table 4). All persons involved in the collection of follow-up data will be independent and blinded to study group allocation.

##### Feasibility and acceptability

Acceptability of the TRIMS education programme will be measured by obtaining qualitative feedback. Possible topics to be explored include ease of understanding; views about the content of the programme and style of delivery; and usefulness and relevance (including cultural relevance). An independent researcher will conduct semi-structured interviews via the telephone. Information about the interviews and a reply slip will be given in person or posted to participants who attend the education sessions. Purposive sampling will be used to select a demographically varied sample of subjects to be interviewed from those who volunteer. Written consent will be obtained in advance by post and confirmed verbally at the time of the interview. Feasibility will be assessed through identification and consideration of problems encountered during implementation of the intervention and uptake will be measured by comparing the number of responses to the number of invitations.

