The aim of The Reversal Intervention for Metabolic Syndrome (TRIMS) study is to investigate the hypothesis that delivery of a group self-management education programme designed to encourage lifestyle changes in individuals identified with MetS would be a feasible, acceptable, and effective strategy for primary prevention of CVD and T2DM. Specific objectives of the study are to: a) develop an evidence based education programme to improve cardiovascular risk and dysglycaemia in people with MetS in primary care; b) determine the impact of attending an education programme on features of MetS and quality of life after 12 months of follow-up; and c) assess acceptability, uptake, and feasibility of implementing a group self-management education programme in an ethnically diverse population of individuals with MetS.

Development, evaluation and implementation of the TRIMS intervention is guided by the most recent Medical Research Council (MRC) Framework for developing and evaluating complex interventions [22]. This article outlines the development, piloting and initial exploratory evaluation of the study intervention. Additionally, the paper describes the design of the main TRIMS study, including the methods used for delivering the trial intervention and for carrying out a definitive evaluation. Baseline data are also reported.

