## Results

Participants were recruited to the main trial between November 2009 and July 2010 (Figure 1). In total, 322 potentially eligible people were invited to participate from 8 different general practices. Of those people who were invited, 40% (n = 129) volunteered to participate, 16% (n = 52) refused, and 44% (n = 141) did not reply. Reasons given by those who declined to participate (n = 52) included lack of time due to work or other commitments (23%), no perceived need for additional advice or health checks (29%), and other health problems (5%). Overall, 82 people were enrolled onto the study, 42 to the intervention group and 40 to the control.

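### Acceptability interviews are offered only to participants who attend the education, so those allocated to it who never come have no stated route to give their views

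*Protocol article*

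**What the plan says.** Objective (c), in the Background of the protocol article, is to "assess acceptability, uptake, and feasibility of implementing a group self-management education programme in an ethnically diverse population of individuals with MetS". The Feasibility and acceptability section gives each of the three parts its own source:

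- **Acceptability:** "Acceptability of the TRIMS education programme will be measured by obtaining qualitative feedback". The interviews are by telephone with an independent researcher. On the approach to participants: "Information about the interviews and a reply slip will be given in person or posted to participants who attend the education sessions". On selection: "Purposive sampling will be used to select a demographically varied sample of subjects to be interviewed from those who volunteer".
- **Feasibility:** "Feasibility will be assessed through identification and consideration of problems encountered during implementation of the intervention".
- **Uptake:** "uptake will be measured by comparing the number of responses to the number of invitations".

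Under Delivery of the TRIMS intervention, participants allocated to the programme are telephoned within 1-2 weeks of baseline and asked to come to sessions in the next 2 months. Under Data analysis, the interview material is analysed thematically with charting, and no acceptability rate or threshold is set.

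**The concern.** The interview frame is conditioned on attendance, which is itself closely tied to acceptability. Someone put off by the venue, the timing, the group format or the perceived relevance of the programme may never come, and the plan gives that person no way to say so. Purposive sampling for demographic variety works only within the volunteers, so it cannot bring in anyone outside the frame.

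Acceptability is part of the study hypothesis in the Background, alongside feasibility and effectiveness. The abstract's conclusion relies on information about acceptability in a multi-ethnic population to support wide applicability. If the themes come only from people who turned up, they describe the experience of the programme well but may say little about why others in the target population would not take it up. The contrast with the effectiveness analysis is worth noting: that analysis is by intention to treat and is meant to keep non-attenders, whereas the acceptability assessment leaves them out.

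**Working it through.** The protocol gives no figure for acceptability, so there is none to reproduce. The check is mainly a comparison of sections, followed by an illustration of size.

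**Step 1. Can an allocated person fail to attend?** Yes. The programme is offered by telephone after randomisation, and nothing makes attendance a condition of staying in the trial.

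**Step 2. Does that person have a route to interview?** None is stated. Information and reply slips go to attenders, and selection is from those who volunteer. The text does not require attendance at both sessions, so someone who came once is not clearly excluded. The gap is for people who came to none.

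**Step 3. Does another source supply their views?**

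- *Uptake.* The Results section reports the responses to the trial invitation: "322 potentially eligible people were invited to participate from 8 different general practices", of whom "40% (n = 129) volunteered to participate, 16% (n = 52) refused, and 44% (n = 141) did not reply". These figures reproduce: 129/322 = 40.1%, 52/322 = 16.1%, 141/322 = 43.8%, and 129 + 52 + 141 = 322. They reach well beyond attenders. But they, and the reasons given by the 52 who declined, concern joining the trial before randomisation. If uptake were instead read as response to the session invitation, it would be a count without reasons.
- *Feasibility.* Problems met during implementation could include non-attendance, but no means of asking non-attenders is described.
- *Pilot.* Under Piloting, the telephone interviews were also with volunteers who had attended. The other pilot sources were session observations and the educators' reflections.

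So no described stage asks people who were offered the programme and did not come about the programme itself.

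**Step 4. Size, as an illustration.** Inputs: 42 randomised to the intervention, 11 of them South Asian (Table 6). Attendance and willingness to be interviewed are not reported, so the rates below are assumptions.

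| Quantity | Arithmetic | Result |
|---|---|---|
| Non-attenders at 10% | 0.10 × 42 = 4.2 | about 4 |
| Non-attenders at 30% | 0.30 × 42 = 12.6 | about 13 |
| South Asian among 4, if proportional | 4 × 11/42 = 1.05 | about 1 |
| South Asian among 13, if proportional | 13 × 11/42 = 3.40 | about 3 |
| Smallest interview pool (60% attend, 30% volunteer) | 42 × 0.60 × 0.30 = 7.6 | about 8 |
| Largest interview pool (100% attend, 80% volunteer) | 42 × 1.00 × 0.80 = 33.6 | about 34 |

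At 60% attendance, 42 × 0.40 = 16.8, so about 17 people would be outside the frame; at full attendance, none would be. The exclusion follows from the wording whatever the rate; only its consequence depends on the rate.

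**The case against.** The best defence is that the frame suits the listed topics. Ease of understanding, content, style of delivery and usefulness can hardly be judged by someone who saw no session, and reasons for staying away belong more naturally with uptake and feasibility. This stands in part: it is why non-attenders should be asked different questions. It does not remove the gap, because neither of the other two measures describes asking them.

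A reader might infer that objective (c) as a whole is answered only by attenders. It is not: uptake and feasibility have separate measures that are not restricted to them.

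A reader might also infer that interviewees have by definition already accepted the programme, so that the answer must be favourable. The documents do not support this. Under Piloting, attenders reported difficulty in grasping the syndrome, and some wanted a more direct style with less group discussion; the curriculum was revised as a result. The planned analysis is thematic, so there is no rate or threshold to bias, and a favourable tilt is likely rather than demonstrated.

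Finally, interviews need consent, so self-selection by volunteering remains even if everyone is approached. That is true, and it limits what the change can achieve.

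**Conclusion.** The point holds for the acceptability part of objective (c) only. As written, acceptability is assessed from participants who attended at least some of the education and then volunteered. Those allocated to the programme who never attend have no stated route to be heard, and the themes may therefore miss reasons for not taking it up.

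The number affected is unknown. About 4 to 13 of 42 is what a non-attendance rate of 10-30% would give, and that rate is an assumption. It would be tempting to add that a large share of the 11 South Asian intervention participants is silenced, but nothing in the documents suggests that non-attendance is concentrated in that group; in proportion, it would be about 1 to 3 of them.

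No stated figure changes, and the primary outcome, the sample size and the intention-to-treat comparison are unaffected. This is an inexpensive improvement to a secondary, qualitative component.

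**What to change.** In the Feasibility and acceptability section:

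1. Send the interview information and reply slip to all 42 participants randomised to the intervention, whatever their attendance.
2. Add attendance (none, one session, both) to the purposive sampling dimensions.
3. Ask non-attenders why they did not come (venue, timing, group format, perceived relevance) rather than about session content.
4. Report the themes by attendance. If few non-attenders respond, state that the acceptability findings apply to attenders only.

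The cost is a wording change, some extra postal slips and a few short calls by the same independent researcher. The downsides are that response among non-attenders will probably be low and that an ethics notification may be needed.
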